## Protocol Deviations

There were two protocol deviations. The Study Protocol deviation was directly associated with the coronavirus disease 2019 (COVID-19) pandemic. During the early part of the trial in 2022, China held on to extremely stringent post-COVID travelling restrictions, as many citizens were still not vaccinated and the country held on to a “zero-infection” policy. This had a tremendous negative impact on the recruitment process of this trial.

Given the circumstances, the Principal Investigator and the study team members estimated the potential drop-out rate may increase to 30% - 40%. After discussing with IRB, we decided to 1) increase the sample size by 40%, from 240 subjects to 340 subjects to account for potential dropouts, and 2) expanded from seven to eight recruiting hospital sites with the addition of Shenzhen Luogang Maternal and Child Health Hospital, in order to facilitate the recruitment of an enlarged sample size. Both protocol deviations were included in this Trial Protocol Version 1.1.

# 1 Background and Rationale

## 1.1 General Introduction

Autism spectrum disorders (ASD) is a genetically heterogenous neurodevelopmental disorder characterized by restricted and repetitive behavioural patterns and persistent deficit in social interaction and communication. Sleep dysfunction, in particular chronic insomnia, is a common comorbidity in children with ASD which occurs at a significantly higher prevalence of 40-80% as compared to 20-30% in typically developing children. Sleep plays a crucial role in regulating behavior and emotions and deprivation of sleep can exacerbate daytime behavioral challenges in children with ASD. This often leading to caretaker burnout who are sleep deprived themselves and profoundly diminish quality of life for all family members.

In recent years, the incidence rate of ASD reported by various countries has been on the rise, for example, according to the United States' Centers for Disease Control and Prevention survey in 2020, 1 in every 36 children aged 8 years in the United States has ASD. In China at present, there is no nationwide statistical survey on the incidence rate of ASD, however, in the 2017 "Report on the Development of China's Autism Education and Rehabilitation Industry II", it is conservatively estimated that there are at least 10 million people with ASD among the 1.3 billion population of China, of which 2 million were children with ASD. The situation of rapidly increasing new cases of ASD worldwide is dire.

## 1.2 Rationale and Justification for the Study

Current guidelines for ASD mainly target patient symptomology and include an individualized treatment solution comprising of a combination of behavioral therapies to improve core symptoms of socio-communicative deficits and pharmacological interventions to manage challenging behaviours and sleep disorders. However, meta-analyses of these interventions show only modest effectiveness with pharmacological interventions invariably causing undesirable side-effects, in addition, behavioral therapies are time-consuming, costly and often require high involvement of caretakers which reduce adherence over the long term^11. As there is no intervention shown to cure ASD, a significant portion of individuals with ASD would require lifelong support, which imposes substantial financial and emotional burdens on their families and substantially heightens societal costs. Hence, there is an urgent need for the development of novel treatments that is safe and with greater efficacy in addressing the core and associate symptoms of ASD.

### 1.2.1 Research findings on pathophysiology of ASD

Decades of research in ASD have revealed that genetic risk factors and environmental factors are significant contributors to the susceptibility of a child developing ASD, however the exact causes of ASD remain unclear. The consensus among most researchers is that ASD symptoms are caused by a lack of interhemispheric coherence and impaired cortical functioning, in particular, dysfunctions in functional connectivity of certain brain regions associated with ASD such as the left dorsal lateral prefrontal cortex (L-dLPFC) that controls executive functioning and social cognition and the cerebellar that is involved in sociolinguistic processing and adaptive predictions in social cognition. These brain alterations occur at the cellular and systems level and may lead to disruptions in excitation/inhibition (E/I) balance as supported by various human studies.

### 1.2.2 Research on existing knowledge of Transcranial Electrical Stimulation and ASD

In recent years, there has been growing interest in the therapeutic potential of transcranial electrical stimulation (tES) as a novel treatment for several pediatric psychiatric and neurological disorders including ADHD, cerebral palsy, dyslexia, and autism spectrum disorder because of its ability to induce long-term potentiation (LTP)-like and long-term depression (LTD)-like effects that is thought to mediate neuroplasticity changes in the central nervous system.

tES is a form of non-invasive brain stimulation technique that transmits low intensity electrical current (<2mA) to specific areas of the brain via surface electrodes that are placed on the scalp to modulate neuronal excitability and spontaneous firing rates. There are different modes of tES according to the electrical output waveform^42, among them, tPCS is the most novel type and has gained increasing attention in experimental settings. Furthermore, in clinical use, tPCS with a fixed frequency of 400Hz, has received health regulatory approval in Singapore for the treatment of limb spasticity in pediatric cerebral palsy since 2022, marking a significant advancement for the use of tPCS in pediatric-centric healthcare compared to other forms of tES.

tPCS delivers pulsed currents at a predetermined frequency to the cortex, as opposed to the direct current provided by tDCS. Studies involving tPCS have demonstrated effects on resting state functional connectivity, reported to facilitate interhemispheric coherence and enhance cortical plasticity. These neural impact of tPCS may be of relevance to ASD since widespread prefrontal-posterior underconnectivity and atypical information processing between brain regions are well-established in this disorder. Furthermore, children with ASD were found to have elevated global excitation-inhibition (E/I) ratio which could serve as a consistent neuromodulatory target in treating ASD across children with heterogenous etiology. EEG bands may act as proxy markers for neural excitation and inhibition and tPCS has been evidenced to increase/decrease EEG band power in a frequency-specific manner, indicating its potential therapeutic application in ASD via modulating highly associated brain regions such as the prefrontal cortex and the cerebellar to target E/I imbalances. In fact, a previous study using mouse models of ASD-linked genes demonstrated that modulating activities of cerebellar-prefrontal circuits improved social impairments and inflexible behaviours, purported to be due to the activation of GABAergic Purkinje cells in the cerebellar Rcrus1 and the posterior vermis.

Finally, in studies involving children with ASD and transcranial direct current stimulation (tDCS), the most common type of tES used in research, positive improvements in ASD evaluation scores have been reported after stimulation of the L-dLPFC, the cerebellar or both the L-dLPFC and the cerebellar. For example, in a study involving 16 ASD children, it was reported that 20 sessions of 20 min, 1 mA prefrontal-cerebellar tDCS stimulation resulted in a significant reduction in severity of ASD global symptoms as measured by the Aberrant Behaviour Checklist (ABC) and the Autism Treatment Evaluation Checklist (ATEC) in the active stimulation group compared to the sham stimulation group. In another small open label, the quality of sleep and mood in participants was reported to have improved, in addition to a 25% reduction in ABC scores.

### 1.2.3 Safety of tES in Children

While there are yet no studies done involving tPCS and children with ASD, the safety of tPCS had been

investigated in childhood cerebral palsy and in adult neurological disorders such as Parkinson's disease, chronic visceral pain and disorder of consciousness, with no adverse events recorded. At present, it is generally considered that an output current between 0-2mA, and the single stimulation time is less than 40 minutes is considered relatively safe. There is no exact guidelines for tES dosing in children although a dose of up to 1mA is typically used. Krishnan C et.al conducted a comprehensive statistical analysis of 48 clinical studies involving more than 513 children and / or adolescents with non-invasive brain stimulation. They found that the most common adverse reaction of tES among people under 18 years of age was skin tingling, with an incidence rate of 11.5%, followed by skin itching, with an incidence rate of 5.8%. These adverse reactions were transient and non-persistent. In terms of cognitive adverse events, treatment-emergent mania and hypomania have been reported in unipolar and bipolar depression treatment in tDCS trials in diseased adults. Finally, drug interactions with tDCS have been reported, with antipsychotics with high D2 affinity such as Haloperidol and Risperidone reported to suppress neuromodulation-induced plasticity while benzodiazepines were associated with an increase in depression scores when used in conjunction with tDCS.

### 1.3 Rationale for Study Purpose

Considering the urgent clinical need to improve core and associate symptoms in children with ASD beyond current treatment options, the demonstrated safety profile and efficacy of tPCS in other vulnerable paediatric populations such as cerebral palsy and promising results in improving social functioning in preliminary small-sample studies of tES in children with ASD, we aim to investigate the effects of tPCS in addition to standard therapy, in improving social functioning, sleep and challenging behaviours in children with ASD aged 3 to 14 years old, in a higher-powered study.

### 1.4 Rational for Study Population

ASD symptoms start in childhood and manifest for a lifetime, potential new interventions for ASD to improve social functioning and associated symptoms should start as an early intervention to leverage on enhanced neuroplasticity that occurs during childhood to optimize any treatments effects.

### 1.5 Rationale for Study Design

The study will be designed as a multi-center, sham-controlled, double-blinded, randomized controlled trial to investigate effects of tPCS in improving social functioning and sleep in children with ASD aged 3-14 years old. Both the intervention and control group will both receive standard of care behavioural therapy for ASD in China (i.e ABA therapy, structured teaching, play therapy and speech therapy). In addition, the intervention group will receive active tPCS stimulation while the control group will receive sham tPCS stimulation, during the period of the trial (20 sessions over one month), this will ensure that any estimated treatment differences between groups is unlikely due to placebo effects. All doctors performing pre-post treatment evaluation will be blinded to the allocation of participants to the two groups, participants and their accompany caretakers will also be blinded, thus it will be a double-blind design. The trial recruitment and execution will take place in eight different sites in the Guangdong province in China, to avoid site-specific bias and to verify the feasibility of tPCS in varying clinical environments with patients from different socio-economic backgrounds. The double blinding, sham-controlled, multi-site design will ensure minimal bias to be introduced that may exert confounding effects to the study results.

## **2 Hypothesis and Objectives**

### **2.1 Hypothesis**

tPCS, in addition to standard behavioural therapy, will improve social functioning compared to standard therapy alone in children with ASD aged 3 to 14 years old. We also hypothesize that tPCS will improve sleep disorders in children with ASD aged 3 to 14 years old when compared to standard behavioural therapy alone.

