### 3.3 Screening Visits Procedures and Recruitment

Potential participants will be children with ASD coming for clinic visit and receiving inpatient and outpatient pediatric psychiatry, neurology and/or ASD therapy services at the eight sites. The study team doctors on duty will be responsible for identifying potential participants and screened according to the diagnostic, inclusion and exclusion criteria as stated in sections 3.4 to 3.6. Screening per participant will take approximately two hours. If criteria are met, potential participants and their parents /legal guardian who show interest in the study will be given relevant information (standard study participation information sheet ) and the consent /assent form (See Appendix 4) in a private room which is comfortable and with privacy to consider carefully. Adequate time will be given to the participant to consider participation. There will be no coercion. Any query will be redirected to the study team doctor on site. Subjects and parents / legal guardians will be informed that participation or not will not affect medical care. If the child has some but not full understanding of the information sheet & consent form, the simplified version (assent form) will be used. However, assent form (between 6 – 14 years old) is omitted if subject is unable to read and understand due to chronic ASD condition. Consent will be taken by anyone from the study team on site. Parents/ legal guardian will sign the consent form in the presence of a witness.

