**Figure 3. Electrode placement for tPCS (Active and Sham)**

#### 6.2.3 Concomitant therapy:

After tPCS, participants in both active and sham-tPCS groups will be given standard behavioural therapy over 4 weeks in the study period. There will be a 1-hour therapy session in addition to daily active or sham tPCS. Standard behavioural therapy includes Applied Behaviour Analysis, structured education, play-based therapy and speech therapy. Each of the four therapies will be administered five times per subject, totaling 20 hours therapy per subject. Standard therapy is performed by experienced therapists with at least five-year experience.

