### 9.2 Statistical and Analytical Plans

#### 9.2.1 General Considerations

Statistical analysis will be implemented using the IBM SPSS version 27.0. Before applying any statistical test, the data sets will be tested for a normal distribution with the Shapiro–Wilk test. If the data was found to be normally distributed, then one- way analysis of variance ANOVA and Student’s t-test will be used for the comparison between groups. Analysis of Covariance ANCOVA will be used to compare one or more means between groups

while controlling for the effects of one or more covariates (continuous variables that are related to the dependent variable). For comparison with the baseline value, paired t-test or one-way analysis of variance (ANOVA) will be used to compare the differences within the group before and after treatment. If the data was found to be not normally distributed then Kruskal-Wallis test or Mann-Whitney rank-sum test was used for the comparison. In order to correct for multiple comparisons, Bonferroni correction will be used to further validate the significance of each p-value. All statistical tests were conducted using a two-sided test. The  $\alpha$ -value was set to 0.05 for all the statistical tests and < 0.01 for Bonferroni correction. Chi-Squared test was used for categorical data, and Mann-Whitney rank sum test was used for ordinal data.

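### Section 2.1 names a comparator that is not in the trial, and the final-analysis plan does not make active minus sham the test of the hypotheses

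*Combined protocol and SAP*

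**What the plan says.** **Hypotheses.** Section 2.1 states the social-functioning hypothesis as tPCS added to behavioural therapy, which "will improve social functioning compared to standard therapy alone in children with ASD aged 3 to 14 years old". The sleep hypothesis has the same comparator: "when compared to standard behavioural therapy alone".

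**Arms.** Section 1.5 describes two arms: "the intervention group will receive active tPCS stimulation while the control group will receive sham tPCS stimulation". Section 6.2.3 adds that "participants in both active and sham-tPCS groups will be given standard behavioural therapy over 4 weeks in the study period", and gives the amount: "Each of the four therapies will be administered five times per subject, totaling 20 hours therapy per subject". No arm receives therapy without a device. Section 1.5 explains that the sham is there so that a difference between groups is unlikely to be a placebo effect.

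**Outcomes.** Sections 2.2 and 2.3 define the ATEC, ABC and CSHQ outcomes as change in mean score from baseline to post-treatment. Neither section names a contrast between arms.

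**Sample size.** Section 9.1 names a paired t-test with an effect size of 0.36 and arrives at 120 per group.

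**Analysis.** Section 9.2.1 lists ANOVA, t-test and ANCOVA between groups. It then says that for comparison with baseline a "paired t-test or one-way analysis of variance (ANOVA) will be used to compare the differences within the group before and after treatment". It does not say which of these tests decides the hypotheses. Appendix section A5.3 does state a between-group null for all three scales, but under the interim analysis.

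**The concern.** Section 2.1 and the design describe two different effects. A comparison with therapy alone would include the placebo response to 20 device sessions; a comparison with sham plus therapy removes it. The data can support only the second, so a conclusion worded as in 2.1 would claim something the trial did not test.

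The remaining sections do not settle which contrast counts. Read literally, a change-from-baseline outcome, a paired t-test in the sample-size section and a within-group test in 9.2.1 fit together as a before-after analysis of the active arm. That analysis cannot isolate tPCS, because the arm's change also carries the behavioural therapy, placebo response, maturation and regression to the mean. As written, the plan leaves it open to present an active-arm improvement, or significance in the active arm only, as the efficacy result.

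**Working it through.** **1. Which test does the plan's own sample size fit?**

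Inputs from section 9.1: effect size (0.20 + 0.52)/2 = 0.36, 80% power, alpha 5%. The section says both two-sided and one-sided, so both are tried.

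- Two-sample, two-sided: n per group = 2(1.960 + 0.842)²/0.36² = 2 × 7.849/0.1296 = 121.1, so 122 (123 with the noncentral t).
- Two-sample, one-sided: 95.4, so 96 (97).
- Paired, two-sided: 7.849/0.1296 = 60.6, so 61 (63).
- Paired, one-sided: 47.7, so 48 (50).

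The stated 120 is close only to the two-sample, two-sided figure. The number is a between-group one, although the text calls the test paired.

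**2. How often is a within-arm test significant when tPCS does nothing?**

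Inputs from the documents: 170 per group (section 4.2), or 170 × 0.6 = 102 per group after the 40% drop-out in section 9.1; two-sided alpha 0.05 (section 9.2.1).

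Assumptions, not in the documents: both arms share the same background change of 0.1, 0.2 or 0.3 SD from therapy, placebo and time; the pre-post correlation r is 0.6 or 0.8; the SD is equal at both visits.

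Formulas: the paired standardized change is dz = change/√(2(1 − r)), and p is the power of the two-sided paired t-test with noncentrality dz√n. The arms are independent, so the chance that active is significant and sham is not is p(1 − p).

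Example: change 0.2, r = 0.6 gives dz = 0.2/√0.8 = 0.224. At n = 102, p = 0.609 and p(1 − p) = 0.609 × 0.391 = 0.238.

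| Change (SD) | r | dz | p, n = 102 | p(1 − p), n = 102 | p, n = 170 | p(1 − p), n = 170 |
|---|---|---|---|---|---|---|
| 0.1 | 0.6 | 0.112 | 20% | 16% | 31% | 21% |
| 0.1 | 0.8 | 0.158 | 35% | 23% | 54% | 25% |
| 0.2 | 0.6 | 0.224 | 61% | 24% | 83% | 14% |
| 0.2 | 0.8 | 0.316 | 89% | 10% | 98% | 1.6% |
| 0.3 | 0.6 | 0.335 | 92% | 7.5% | 99% | 0.8% |
| 0.3 | 0.8 | 0.474 | 99.7% | 0.3% | over 99.9% | under 0.1% |

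The active arm's paired test is significant in 20% to over 99% of such trials. The active-only pattern occurs in under 1% to 25%; 25% is also the mathematical ceiling of p(1 − p), reached at p = 0.5.

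**3. The between-arm test under the same assumptions.** Both arms have the same expected change, so active minus sham has expectation zero whatever the background change. The test rejects at its nominal 5% in every row.

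**The case against.** The other side has a good case on several points.

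- **Therapy cancels between arms.** A reader might infer that, because no arm gets therapy alone and every child gets 20 hours of it, tPCS will be credited with the therapy's effect. The documents do not support that. The same therapy is given in both randomized arms, so its effect drops out of active minus sham. The absent therapy-alone arm causes no such bias, and sham plus therapy isolates the stimulation better than therapy alone would.
- **The therapy is not shown to be new.** Section 1.5 calls it standard of care, and section 3.3 recruits from children "receiving inpatient and outpatient pediatric psychiatry, neurology and/or ASD therapy services at the eight sites". Nothing says that the 20 hours are additional to what a child already received.
- **Between-group tests are planned.** Section 9.2.1 lists them first, A5.3 states a between-group null, and the sample size fits a between-group comparison. Change from baseline is an ordinary outcome definition, and no section says that a within-arm p-value will support a claim for tPCS.
- **The within-arm percentages are power, not error rates.** If an arm truly changes by 0.2 SD, a significant paired test is correct about that change. The figures matter only if the test is read as evidence for tPCS. The active-only pattern is also below 5% in several rows.

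All of this stands, and it limits the point to wording and designation. It does not remove it. The comparator in 2.1 still does not match the control arm, the one explicit between-group null sits in the interim section, and the within-group tests are not labelled descriptive.

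**Conclusion.** The point holds as a defect in the hypothesis wording and in the designation of the confirmatory contrast. The randomized sham design itself is sound for active versus sham, and no third arm is needed.

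The documents alone establish that the 2.1 comparator is absent from the trial, and that sections 2.2, 2.3, 9.1 and 9.2.1 do not fix active minus sham as the test of the hypotheses. The size of the risk rests on the assumed background change and correlation. It is conditional on a within-arm result being read as efficacy, which the plan permits but does not announce. Under those assumptions such a reading would favour an inert device in 20% to over 99% of trials if the active arm's test alone is used, and in under 1% to 25% if the active-only pattern is used, against 5% for the between-arm test. It should be corrected because it determines what the trial may conclude.

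**What to change.** - **Section 2.1:** state both hypotheses as active tPCS plus standard therapy compared with sham tPCS plus standard therapy.
- **Sections 2.2 and 2.3:** define the effect for ATEC, ABC and CSHQ as the active-minus-sham difference at Visit 22.
- **Section 9.2.1:** make the between-group ANCOVA of post-treatment score on arm and baseline score the test of the hypotheses. Report within-arm change as mean and 95% CI, and state that no conclusion on tPCS rests on it.
- **Section 9.1:** replace paired with two-sample and state two-sided throughout. The stated 120 per group already roughly fits (122 at 0.36, two-sided 5%, 80% power).

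Cost: wording only. No new arm, visit or data are needed, and ANCOVA is already among the planned methods. The report loses within-arm p-values, and the claim is limited to superiority over sham. Whether 340 recruits are enough for 40% drop-out is a separate question that this change does not settle.
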